### Study intervention

All Participants who are eligible and consented to participate in the study shall receive PA promotion content in accordance to the Swedish model [23]. This method consists of five core components: (1) person-centered health promotion consultation; (2) a written prescription of physical activity; (3) a prescription guided by evidence-based knowledge on physical activity in the prevention and treatment of health conditions; (4) a follow-up of the written prescription; and (5) collaboration between the healthcare service and physical activity organizers outside healthcare. It is also emphasized that the method should be tailored to the local conditions in healthcare organizations. More specifically, we will recommend PA and provide informative flyers according to the Portuguese National Healthcare Authority and the World Health Organization recommendations for older age people. In addition to PA promotion counseling, all patients will be randomly allocated to either the intervention or the control groups using block randomization generated by a computer-generated random number sequence^1^. The allocation sequence will be generated by a research assistant who will not be involved in the data collection process. Eligible participants will be randomly assigned in a 1:1 ratio to one of the following intervention arms: Arm A (experimental arm), use of the device activity watch (Fitbit Sense), and a sleep monitoring mattress (Withings SA, France - Sleep Analyzer); Arm B (control): non-use of the devices. Participants randomized to wearable device BCT (Arm A) will be provided goal setting, self-monitoring and feedback. On the first visit they will undergo a brief training session where they’ll learn how to effectively use both devices, sync their data, and interpret the feedback they receive. Arm A participants will receive weekly feedback based on their activity and sleep data trough their devices. This might include suggestions for increasing step counts or tips for better sleep hygiene. The study team will provide a communication channel available for participants to address any technical issues or queries they might have regarding device usage. They will be instructed to wear the wearable device all the time (except when charging) and use the mattress while sleeping. Patients who do not use the device for at least 60% of the time will be excluded from the trial. Compliance of divide use will be regularly monitored by the study team.

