### Design and setting of the study

This study will be an open-label randomized control trial, reported in line with the Consolidated Standards of Reporting Trails (CONSORT) statement and checklist and Template for Intervention Description and Replication (TIDieR) checklist [20, 21]. Participants will be recruited through primary care and specialist outpatient clinic at Hospital da Luz Lisboa, a private tertiary hospital in Lisbon, Portugal.

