**Fig. 1 Fig1:**
[figure not shown]
SPIRIT diagram

The primary outcome will be the participants’ PA measurement assessed at baseline and at 6 months using the IPAQ-SF. Secondary outcomes will include changes in participants’ frailty status, biometric measurements, quality of life, and biopsychosocial assessments at baseline and at 6 months (Table 1).

**Table 1 Tab1:** Data measurements to be recorded during the study period

	Baseline	Study period	6 month follow-up
**Self-reported**	IPAQ-SF		IPAQ-SF
	IMSA		IMSA
	SF-12		SF-12
**Healthcare professional reported**	Vivifail questionnaire		Vivifail questionnaire
	BMI		BMI
	Abdominal perimeter		Abdominal perimeter
	Calf perimeter		Calf perimeter
**Sensor data**		Number of steps	
		Heart rate	
		Sleep quality	
**EHR data**	Historical clinical data	Unplanned hospital admissions	

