### Statistical analysis

A sample size of 40 participants per arm was calculated to be sufficient to detect a group difference, with the alpha set at 0.05, and the power set at 0.80. Protecting against a dropout rate of 20% over the 6-month study duration, 50 participants will be recruited and randomized into each arm (A or B). We will conduct an exploratory analysis of the recorded data. This will be based on descriptive statistics and will be used to characterize the universe of data and identify outliers and general trends. Agreement between IPAQ-SF and wearable activity will be assessed trough Cohen’s kappa. We will use McNemar’s test to compare groups at baseline and 6-month follow-up regarding the study outcomes. In addition, we will assess the impact of wearable data and PROMs in predicting unplanned hospital admissions using classification accuracy, absolute error, and ROC AUC analysis.

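### The 60% device-use rule removes participants after randomisation from Arm A only, so it breaks the randomised comparison; the direction and size of any bias are not known from the document

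*Protocol article*

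**What the plan says.** All references are to the protocol article.

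- **Allocation (Study intervention).** "Eligible participants will be randomly assigned in a 1:1 ratio to one of the following intervention arms". No run-in with the devices before randomisation is described.
- **Who has a device (Study intervention).** The experimental arm is "Arm A (experimental arm), use of the device activity watch (Fitbit Sense), and a sleep monitoring mattress"; the comparator is "Arm B (control): non-use of the devices".
- **The rule (Study intervention).** "Patients who do not use the device for at least 60% of the time will be excluded from the trial". The next sentence reads "Compliance of divide use will be regularly monitored by the study team", which places the rule during follow-up.
- **Primary outcome (Study measures and outcomes).** "The primary outcome will be the participants’ PA measurement assessed at baseline and at 6 months using the IPAQ-SF". This is a questionnaire completed in both arms.
- **Sample size (Statistical analysis).** 40 per arm at alpha 0.05 and power 0.80, raised to 50 per arm: "Protecting against a dropout rate of 20% over the 6-month study duration". The section does not say whether people removed under the 60% rule count towards that 20%.

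The article does not say that anyone removed under the rule is still followed to 6 months or analysed as randomised.

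**The concern.** Controls have no device, so the rule can sensibly reach only Arm A; read literally it would remove every control. It acts after allocation and selects on behaviour that the allocation itself creates. Arm A would be reduced to people who took up the intervention, while people of the same disposition in Arm B stay in. The comparison becomes one of device users with all controls, which is not the effect of offering the device on top of activity promotion.

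People who use the device little may be less motivated, frailer or less well. Each of these could bear on later activity, frailty and quality of life, so the harm is not confined to the primary outcome.

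The wording is exclusion from the trial, not from a per-protocol or sensor-data set. If it is applied as written, the 6-month outcomes of those removed may never be collected, and no later choice of analysis set could restore them. The rule is also unnecessary for the main comparison, because the IPAQ-SF does not need a device.

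**Working it through.** **1. The plan's own figure.** 40 / (1 − 0.20) = 50 per arm, as stated. The 40 itself cannot be rebuilt, because the article gives no effect size, SD or event rates.

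**2. A scale for the illustration.** Back-solving 40 per arm at 80% power, with alpha 0.05 taken as two-sided:
- normal approximation: (1.960 + 0.842) × √(2/40) = 0.626 SD;
- t test: 0.634 SD.

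This is a derived yardstick (about 0.63 SD), not a difference that the sponsor planned for.

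**3. Shift in Arm A's mean when there is no true effect.** Let q be the fraction of Arm A removed (those with the lowest device use) and ρ the correlation between propensity to use the device and 6-month activity. Both are assumptions; the article gives neither. For a bivariate normal,

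shift = ρ × φ(z_q) / (1 − q), in SD units.

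The multiplier φ(z_q)/(1 − q) is:
- q = 0.10: 0.1755 / 0.90 = 0.195
- q = 0.20: 0.2800 / 0.80 = 0.350
- q = 0.40: 0.3863 / 0.60 = 0.644

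**4. Type I error.** Noncentral t, two-sided 5%, outcome SD set to 1. Arm A has 40 × (1 − q) analysed (20% dropout in both arms, then the exclusions) and Arm B has 40.

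| Removed (q) | Analysed A vs B | ρ | Shift (SD) | Type I error |
|---|---|---|---|---|
| 10% | 36 vs 40 | 0.1 | 0.1 × 0.195 = 0.02 | 5.1% |
| 20% | 32 vs 40 | 0.3 | 0.3 × 0.350 = 0.105 | 7.2% |
| 40% | 24 vs 40 | 0.3 | 0.3 × 0.644 = 0.193 | 11.4% |
| 40% | 24 vs 40 | 0.4 | 0.4 × 0.644 = 0.26 | 16.6% |

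In the 20%, ρ = 0.3 row, 6.4 of the 7.2 percentage points are false findings in favour of the device, against 2.5 nominally. With ρ = 0 the shift is zero and the error stays at 5%. With ρ = −0.3 the shift is −0.06 SD at 10% removed and −0.19 SD at 40%, against the device.

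**5. Numbers and power, if the exclusions come on top of the 20% dropout.** With 20% removed, Arm A has 50 × 0.80 × 0.80 = 32. Power at 0.634 SD for 32 vs 40 is 75%, against 80% for 40 vs 40. If the 20% already covers these people, 40 is kept and there is no such loss.

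**6. What retention costs.** If those below the threshold stay in and gain nothing, the mean difference shrinks by the factor (1 − q). At 40 per arm:
- 10% non-users: 0.634 × 0.90 = 0.571 SD, power 71%;
- 20% non-users: 0.634 × 0.80 = 0.507 SD, power 61%.

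**The case against.** Several points can fairly be made on the other side.

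- **Direction.** A reader might infer that the rule inflates the device's effect. The article does not support that as a fact: it gives no link between device use and 6-month IPAQ-SF. Bias towards the device is plausible because low users receive less of the intervention, but at zero correlation there is no bias and at a negative one it reverses. This limit stands.
- **The illustration is not the planned test.** The Statistical analysis section names McNemar's test and gives no effect size or SD. The t-test figures show an order of magnitude only. This stands.
- **Arm A below 40.** A reader might infer that the planned 40 will be missed. That follows only if the exclusions add to the 20% allowance; non-users and dropouts may largely be the same people. This stands.
- **Hospital stays.** A reader might infer that the rule deletes the unplanned admissions under study. The article fixes no time base for the 60%. Judged over about 182 days, falling below it needs more than 0.40 × 182 ≈ 73 days without use, whereas a one-week stay is 7/182 ≈ 4%. Admissions are also taken from health records, not the device. The inference is weak unless the window is short.
- **Statement that all participants have two visits (Study measures and outcomes).** This might be read as keeping low users in follow-up. Someone excluded from the trial is no longer a participant, so it does not settle the matter.
- **An unseen analysis plan.** It may define an as-randomised set. It could not supply 6-month data from people no longer followed, and the exclusion rule is fixed in the article, not left open.

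None of these points rescues the rule itself.

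**Conclusion.** The structural fault follows from the article's text and rests on no numerical assumption: the rule is a post-randomisation, adherence-based exclusion that can apply to one arm only, and it removes the protection of randomisation for every outcome. It should be corrected before participants are lost under it.

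The consequence is conditional. Over correlations of 0.1 to 0.4 and 10% to 40% of Arm A removed, the illustrative bias runs from negligible (0.02 SD, about 5% type I error) to substantial (0.26 SD, about 17%). The correlation, the fraction removed and the t test are all assumptions. The supportable statement is that the rule can bias the result, most plausibly towards the wearable. The fall in power from 80% to 75% applies only if the exclusions are additional to the dropout allowance.

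**What to change.** Replace the sentence in Study intervention with wording such as: *All randomised participants remain in the trial, are asked to attend the 6-month visit and are analysed in the arm to which they were assigned, whatever their device use. Device use is reported as a measure of adherence.*

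Keep the 60% threshold only for sensor-data analyses, such as agreement between IPAQ-SF and wearable activity, or for a supplementary analysis labelled as such. State which device it refers to (watch, mattress or both) and the window over which it is judged. If a complier-type analysis is considered, note that people below 60% still receive training, goal setting and some feedback. Assuming that assignment has no effect on them would be doubtful.

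**Cost.** One sentence, and the effort of bringing low users back at 6 months. The 50 per arm still follows arithmetically from 40 and 20% dropout. The effect estimate will be diluted by non-users: on the assumption that they gain nothing, power at about 0.63 SD with 40 per arm is 71% with 10% non-users and 61% with 20%. That should be acknowledged where the power is stated. It is a reason to look again at the sample size, not to remove the non-users.

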### Study measures and outcomes

All participants will have two study visits: baseline and after 6-month follow-up (Fig. 1). Measurements will include self-reported data: IPAQ-SF, INTERMED-Self Assessment (IMSA) and Short Form Health Survey (SF-12); study team measurements: Vivifrail test^2^, Body Mass Index (BMI), abdominal perimeter and calf perimeter measurements; and Electronic Health Records (EHRs) information retrieval (diagnoses, medications, and unplanned health visits before and during the study period). Information on the treatment allocation will not be provided to the data collectors. The data collection forms only contain unique identifier codes assigned to each participant.

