### Inclusion and exclusion criteria

Patients may be included if they are more than 65 years old and have MM. We will use a previously proposed definition of MM as the presence of two or more of the following chronic conditions: hypertension, depression or anxiety, chronic musculoskeletal conditions causing pain or limitation, arthritis and/or rheumatoid arthritis, osteoporosis, asthma, chronic obstructive pulmonary disease (COPD), ischemic heart disease, peripheral artery disease, heart failure, cerebrovascular diseases, chronic stomach or colon conditions, chronic hepatitis, diabetes mellitus, thyroid disorders, any active cancer in the previous five years, chronic kidney disease, chronic urinary conditions, hyperlipidemia, and obesity [22]. In addition, participants must have access to their smartphones. Exclusion criteria will include: patients who are sufficiently physically active, defined with International Physical Activity Questionnaire - Short Form (IPAQ-SF) > 150 min aerobic physical activity per week, an existing absolute contraindication for PA according to the American College of Sports Medicine (acute myocardial infarction within two days, ongoing unstable angina, uncontrolled cardiac arrhythmia with hemodynamic compromise, active endocarditis, symptomatic severe aortic stenosis, decompensated heart failure, acute pulmonary embolism, pulmonary infarction, deep venous thrombosis, acute myocarditis or pericarditis, acute aortic dissection, physical disability that precludes safe and adequate testing), poor comprehension of Portuguese language, disabling neurological disorder (defined as mRankin score $$\ge$$ 4), severe psychiatric illness, learning disability, dementia and cognitive impairment, registered blind, housebound or resident in a nursing home, non-ambulant, advanced cancer, and scheduled for surgery within five months after the first consultation. Orthopedic or rheumatologic diseases with severe impairment and chronic pain syndromes with inherently reduced mobility will also not be included.

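### The self-reported outcomes are scheduled only at baseline and one 6-month visit, and dropout is met only by extra recruitment; collecting the 6-month questionnaires remotely from those who stop would protect comparability cheaply

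*Protocol article*

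**What the plan says.** All references are to the Protocol article.

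- **Study measures and outcomes.** The schedule is "All participants will have two study visits: baseline and after 6-month follow-up". The primary outcome follows it: "The primary outcome will be the participants’ PA measurement assessed at baseline and at 6 months using the IPAQ-SF". Table 1 lists the IPAQ-SF, IMSA and SF-12 as self-reported, at baseline and 6 months, and leaves the column between them empty for all three. Only sensor data and unplanned hospital admissions are recorded in between.
- **Study intervention.** Arm B does not use the devices. Arm A participants whose device use falls below 60% of the time are to be excluded from the trial. Arm B has no corresponding rule.
- **Statistical analysis.** Loss to follow-up is handled in one sentence, which begins "Protecting against a dropout rate of 20% over the 6-month study duration" and raises 40 per arm to 50. McNemar's test is named for comparing the study outcomes at baseline and 6 months.
- **Inclusion and exclusion criteria.** As a condition of entry, "participants must have access to their smartphones".

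**The concern.** With a single post-baseline assessment, anyone who leaves before month 6 and is not followed further has no post-baseline primary outcome. Nothing else collected can stand in for it in the comparison of arms: step counts exist only in Arm A, and McNemar's test needs both members of the baseline and 6-month pair.

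Recruiting more people replaces the number lost, not the people lost. Participants are over 65 with multimorbidity, so illness or loss of motivation can plausibly lower both activity and attendance. The trial is open-label, and both the burden of wearing a device and the 60% exclusion fall on Arm A alone. The mix of people who remain could therefore differ between arms. No later analysis plan can recover a questionnaire that was never requested.

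The loss looks partly avoidable, because all three instruments are self-reported and every participant has smartphone access.

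**Working it through.** **Inputs from the Protocol article:** 40 per arm before dropout, alpha 0.05 (sidedness not stated), power 0.80, dropout 20%, 50 randomised per arm (Statistical analysis); 1:1 allocation and the 60% device-use rule (Study intervention); two assessment times (Study measures and outcomes, Table 1). No effect size or standard deviation is given, so results are in SD units and rest on assumptions marked as such.

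**1. The plan's own figure.** 40 / (1 − 0.20) = 50 per arm. This reproduces exactly.

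**2. Participants without a 6-month value at the planned rate.** 0.20 × 50 = 10 per arm, 20 of 100 in total. The 40 left per arm equal the calculated requirement, so the stated power already allows for this loss. Arm A exclusions for low device use would come on top unless the 20% was meant to cover them; the article does not say.

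**3. What extra recruitment leaves untouched.** In each arm let p be the fraction without an outcome and δ the mean activity of completers minus that of dropouts. The full-arm mean is (completer mean) − p × δ, so a comparison of completers is off by

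bias = p_A × δ_A − p_B × δ_B (positive favours the wearable).

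The number randomised does not appear in this expression. With p = 0.20 in both arms it becomes 0.20 × (δ_A − δ_B):

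| Assumed δ_A − δ_B (SD) | Bias (SD) |
|---|---|
| 0 | 0 |
| ±0.25 | ±0.05 |
| ±0.5 | ±0.10 |
| ±1.0 | ±0.20 |

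The documents favour no row and neither sign. If p differs between arms, as the one-arm exclusion could cause, the bias is (p_A − p_B) × δ even when δ is the same in both.

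**4. Scale.** Assuming a two-sided comparison of two means, 40 per arm at 80% power corresponds to (1.96 + 0.84) × √(2/40) = 0.63 SD. A bias of 0.10 SD would be about 16% of that (0.10 / 0.63). This is only a yardstick, because the test the article names is McNemar's.

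**5. What recovered outcomes could add.** On the same assumption, with a true difference of 0.63 SD:

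| Dropouts recovered | n per arm | Power | Confidence interval width relative to n = 40 |
|---|---|---|---|
| none | 40 | 80.0% | 1 |
| half | 45 | 84.4% | √(40/45) = 0.943 |
| all | 50 | 87.9% | √(40/50) = 0.894 |

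The last row is a ceiling. Participants who die or withdraw consent to data cannot be recovered.

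**The case against.** The strongest reply is that this argues from silence. The article fixes when the questionnaires are completed, not how. It does not say that they must be completed in person, that a missed visit ends data collection, or that people who stop are not pursued. Retention procedures are commonly left to the full protocol, which is not shown, and two-point assessment is an ordinary design. Entry criteria already exclude housebound and non-ambulant people, the 20% is a planning allowance, and dropout is not defined.

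Much of this stands. There is no contradiction or arithmetic error, and the full protocol may already provide for remote completion. What remains is that the article's positive statements all point one way: one 6-month visit, a dropout allowance met only by more recruitment, and exclusion from the trial for low device use in Arm A. Followed as written, those who stop are replaced rather than followed.

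Three stronger readings are tempting, and the documents do not support them:

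- A reader might infer that the trial is underpowered. It is not on this account: the allowance leaves the calculated 40 per arm.
- A reader might infer a bias towards the wearable. That requires Arm A dropouts to be less active relative to completers than Arm B dropouts are; nothing in the article establishes this.
- A reader might infer that early leavers get a shorter record window and count as free of unplanned events. The text refers only to "unplanned health visits before and during the study period". It neither truncates the window for early leavers nor scores them as non-events, and the Statistical analysis section uses unplanned admissions as a prediction target, not as a comparison of arms.

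**Conclusion.** The point holds as a weakness of the assessment schedule that is cheap to remedy. The primary outcome has one post-baseline opportunity, and the article's only stated answer to losing it is a larger sample, which preserves nominal power but not comparability. The 60% rule adds a route to missing outcomes that exists in Arm A only.

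At the planned dropout rate, up to about 10 of 50 per arm may lack a post-baseline primary outcome; how many of these could be recovered is unknown. The bias figures illustrate what assumed differences would do and are not estimates. The bias is zero if dropouts differ from completers by the same amount in both arms and dropout rates are equal. The power and precision gains rest on a two-sided comparison of means that the article does not specify.

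**What to change.** - **Study intervention and Study measures and outcomes, both sections.** State that stopping the device or missing the 6-month visit does not end outcome collection. The 60% rule must be reconciled with this; changing only the measures section would leave the two in conflict.
- **Collection.** Obtain the 6-month IPAQ-SF, SF-12 and IMSA by telephone or smartphone form, within the 6-month window, from every randomised participant in either arm who stops or cannot attend and has not withdrawn consent to data. Record the mode of completion. Keep the data collector unaware of allocation, which a telephone conversation could otherwise reveal.
- **Analysis.** Keep these participants in their randomised arm and examine mode of completion descriptively. An analysis restricted to in-person forms would not settle the mode question, because it restores the comparison of attenders that is in doubt.
- **Optional clarification.** State a fixed six-month record window from randomisation for unplanned events in all randomised participants.

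The cost is a short amendment and remote questionnaires for about 20 people at the planned dropout rate, plus any low device users not counted in that allowance. No new instrument is needed. The downside is a mixed mode of completion for some participants.

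### Withholding allocation from data collectors is probably ineffective at the 6-month visit, because Arm A is told to keep the watch on almost constantly

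*Protocol article*

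**What the plan says.** The design is declared plainly in the Protocol article, Design and setting of the study: "This study will be an open-label randomized control trial".

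Study measures and outcomes then adds a limited safeguard for outcome collection: "Information on the treatment allocation will not be provided to the data collectors", followed by "The data collection forms only contain unique identifier codes assigned to each participant". The same section schedules two visits, at baseline and at 6 months. It divides the measurements into self-reported ones (IPAQ-SF, IMSA, SF-12), ones taken by the study team (Vivifrail, BMI, abdominal and calf perimeters) and record retrieval. IPAQ-SF is the primary outcome; frailty status and biometric measurements are secondary.

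On the devices, Study intervention says of Arm A: "They will be instructed to wear the wearable device all the time (except when charging) and use the mattress while sleeping". The comparator is "Arm B (control): non-use of the devices". The behavioural content is also confined to Arm A: "Participants randomized to wearable device BCT (Arm A) will be provided goal setting, self-monitoring and feedback", and "Arm A participants will receive weekly feedback based on their activity and sleep data trough their devices".

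The Statistical analysis section plans a kappa statistic for agreement between IPAQ-SF and wearable activity.

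**The concern.** Not handing over the allocation and coding the forms stop staff from learning the arm on paper. They do not stop staff from seeing a watch on a participant's wrist. If one arm attends the 6-month visit wearing the study watch and the other does not, whoever holds the tape or runs the frailty test can usually tell the arms apart. Knowledge of the arm can influence measurements that leave room for encouragement, technique or judgement. The outcomes at stake are the staff-measured secondary ones.

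A second, smaller issue concerns the primary instrument. Arm A would have its own activity record to hand while completing a recall questionnaire, and Arm B would have no trial device to consult. Direct look-up during completion would also affect the kappa analysis: a participant who reads the device and then fills in the IPAQ-SF is partly copying one measurement into the other, and agreement would look better than two independent measurements would show.

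**Working it through.** No arithmetic settles this point; it rests on reading the two sections together.

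1. **What the safeguard covers.** Study measures and outcomes names two steps: allocation is not given to data collectors, and forms show codes only. Both control information on paper. Neither concerns what is visible at a face-to-face visit.

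2. **What is visible.** Study intervention has Arm A wear the watch continuously apart from charging, and gives Arm B none. It also excludes participants whose device use falls below 60% of the time. As written, therefore, the Arm A participants who reach the 6-month assessment are mainly people who wear the watch.

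3. **Whether anything removes the cue.** No section says that the watch is taken off, covered or returned before the 6-month visit. Table 1 lists sensor data only under the study period and not at the 6-month column, but it does not say when wear ends or when devices are handed back.

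4. **Who measures.** The article uses the same term, study team, for those who take the physical measurements, those who run the support channel for device problems and those who monitor compliance. The one separation of roles it states is that the person generating the allocation sequence takes no part in data collection. That protects the sequence and does not bear on what staff see at follow-up.

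5. **Which outcomes are exposed.** Assessor awareness bears on Vivifrail and the perimeters. It bears on the self-reported questionnaires only where staff help with completion. For the IPAQ-SF the relevant feature is the participant's own access to device data: Arm A is trained to interpret its feedback and receives it weekly.

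6. **Size.** The article gives no figure for reporting or observer bias. Its only related arithmetic is the sample size: 40 / (1 − 0.20) = 50 per arm, which reproduces. The 40 per arm comes without an effect size or standard deviation, so there is no stated target difference against which to scale a bias.

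**The case against.** **The trial is open-label and never says blinded.** This stands. A reader might infer that the article claims masked assessment and that the claim is false. The documents do not support that: they promise only that allocation is not supplied. The fault is a safeguard unlikely to do its job.

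**The watch at the visit is an inference.** This also stands in part. The article does not say that the watch is worn at the 6-month visit. Some watches may be charging, and nothing in the eligibility criteria bars a control from owning a tracker, so a watch is not a perfect marker of allocation. The inference is still strong, because it follows from the printed wear instruction. The supportable wording is that most Arm A participants would probably be recognisable.

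**Visit logistics belong in the full protocol.** This is fair as far as missing detail goes. The point, however, does not rest on a gap: one printed instruction works against another printed safeguard.

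**The asymmetry in self-report is the intervention itself.** Largely right. Self-monitoring and feedback are what is being tested, and six months of feedback will inform Arm A's answers whatever happens at the visit. A reader might infer that setting the watch aside would protect the primary outcome fully. It would prevent look-up during completion and nothing more. That participants would actually read the device while answering is possible but not stated.

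**Observer dependence is assumed.** The article does not describe the Vivifrail components, and Table 1 calls it a questionnaire. That limits how firmly the consequence can be stated.

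A reader might also infer a fault at baseline. The documents do not show one: the IPAQ-SF is needed to judge eligibility, and only eligible participants are randomised.

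**Conclusion.** The point holds in a limited form. As printed, keeping allocation from data collectors is likely to be ineffective at the 6-month visit for Vivifrail and the perimeters, because the wear instruction makes most Arm A participants recognisable. This assumes that the watch is still worn at that visit and that no unprinted procedure removes it.

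For the IPAQ-SF, direct look-up is a possible and avoidable source of difference between arms, and it would make the planned kappa less than a comparison of independent measurements. The wider reporting asymmetry is inherent in the intervention and has to be acknowledged.

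A reader might want to express the bias as a share of the detectable difference. The documents do not support any such percentage, since both the bias and the effect size would have to be assumed. Direction is equally open: knowledge of one's own data could reduce over-reporting in Arm A and hide a benefit, or prompt fuller reporting and create one. This is a cheap improvement worth making; it does not undermine the design.

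**What to change.** Add one instruction for the 6-month visit:

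- On arrival, Arm A participants hand watch and phone to an existing staff member who is not the data collector.
- Participants are asked not to mention the device.
- IPAQ-SF, IMSA and SF-12 are completed without consulting device data.
- Vivifrail and the perimeters are then taken, still without the watch.

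If this cannot be arranged, replace the sentence on withholding allocation with a statement that these outcomes are assessed unmasked. In either case, list as a limitation that Arm A reports its activity after six months of device feedback and Arm B does not.

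The cost is about an hour of lost wear data per Arm A participant (an estimate, since the article gives no visit length). No extra procedure or additional staff member is needed.
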